### 2.5. Participants

The project coordinator will invite all toddlers (18 months–2.4 years) and preschoolers (2.5 years–4 years) to participate, and those whose parents/guardians provide written consent will be eligible to participate in the study. Childcare providers and directors from randomly selected childcare centres will also be invited to participate. Participants will receive a small token of appreciation as thanks for their time. See Table 1 for complete inclusion/exclusion criteria for the Childcare PLAY Policy study.

### 2.6. Development and Implementation of the Childcare PLAY Policy

To promote policy engagement, buy-in, and suitability, the policy was developed by our research team in collaboration with an advisory committee that included childcare organizations and centre administrators, childcare providers, municipal childcare stakeholders, and a policy expert. The policy was created following a review of relevant literature on the importance of outdoor play [32], unstructured activity [29,33], and informed by the Canadian 24-Hour Movement Guidelines for the Early Years (0–4 years; [3]). The current version of the policy includes eight statements that are designed to provide specific recommendations for time in energetic play (i.e., minimum of 40 min/day), outdoor time (i.e., 120 min/day), and suggests short (i.e., 15–30 min), frequent (i.e., 3–4 times/day) outdoor periods during childcare hours. It requires that children be exposed to a variety of indoor and outdoor physical activities to promote physical literacy and recommends appropriate role modelling of screen-based technology, with no screen time permitted for children during childcare hours. Sustained sedentary time is recommended to be disrupted and replaced with physical activity. See Appendix A for the Childcare PLAY policy.

Experimental Condition. For eight weeks, childcare providers in the experimental centres will be asked to implement the written policy that outlines optimal physical activity daily affordances and sedentary time recommendations during childcare. Prior to the eight-week intervention period, childcare providers will participate in a training session, led by the project coordinator. The session will last approximately an hour in length, which will detail the characteristics of the study design, review the policy, its implementation, and study tools (e.g., accelerometer logs).

Control Condition. Childcare centres randomly assigned to the control group will be asked to continue their typical daily curriculum for the duration of the eight-week intervention and follow-up period. Upon completion of the study, all centres allocated to this group may opt to receive a copy of the written physical activity policy and the training regarding its implementation.

### 2.7. Measures

A variety of tools will be used to assess the feasibility and effectiveness of the Childcare PLAY Policy (Table 2).

Demographic Information (Parents and Childcare Providers). Parents of participants will be asked to complete a demographic questionnaire at baseline to describe participants and their families (e.g., children’s age, sex, ethnicity, family income, parental education), as well as the children’s physical activity participation outside of childcare (e.g., organized sport or activities). Parental/guardian weekly engagement in MVPA and their view of themselves as a physical activity role model will be measured. Childcare providers and directors will complete a demographic questionnaire at baseline to capture information related to their age, sex, employment status, years of childcare experience, and level of education. Childcare providers will also report time in MVPA and their view of themselves as physical activity role models. No personal identifiers will be stored with participant data.

Physical Activity (Children). Toddlers’ and preschoolers’ physical activity will be measured using ActiGraph™ (ActiGraph, LLC, Pensacola, Florida) accelerometers—the gold standard for measuring young children’s sporadic physical activity patterns in field settings [34,35,36]—for five consecutive days, during childcare hours only. This process will be undertaken pre-intervention (week 0), mid-intervention (week 4), post-intervention (week 9), and at six-month follow-up. Raw data will be collected to capture the sporadic activity and intermittent periods of rest of the young participants. The accelerometers will be worn on the right hip (above the iliac crest) and will begin collecting activity data on the morning of the first day of data collection. Wear-time of the accelerometers (i.e., the time when it is fitted and removed from each child) will be recorded for each participating child by childcare providers using a daily log. Validated and age appropriate cut-points will be applied to the data to delineate the different activity intensities [37].

Anthropometric Measures (Children). Height (using a Seca 214 “Road Rod” Portable Stadiometer; nearest 0.1 cm), weight (using a Tanita 700-TBF300GS Body Fat Analyzer w/Goal Setter scale; nearest 0.1 kg), and waist circumference (using a measuring tape; nearest 0.1 cm) will be assessed at baseline. The data collected will be used to calculate the child’s standardized body mass index score (BMI-z).

Policy Adherence Log (Childcare Providers). A log will be completed by childcare providers three times per week (i.e., Monday, Wednesday, and Friday) to monitor adherence to each statement of the policy during the eight-week intervention period. Childcare providers will check “yes” to indicate that they adhered to the policy statement, “part” to indicate that they only partially followed the policy item, and “no” to indicate that the policy statement was not followed on that particular day. Reasons the policy was not followed will also be indicated from a list of options (i.e., weather, ratios, no space, behaviour, other).

Self-Efficacy (Childcare Providers). To gauge potential changes in childcare providers’ self-efficacy to provide physical activity opportunities and overcome related barriers, a 40-item instrument was developed for the purpose of the study, which will be administered twice at baseline (to assess test, re-test reliability) and at all subsequent time points. Childcare providers will rate their confidence to each item on a scale from 0 (I am not at all confident) to 10 (I am highly confident) in line with the construction of self-efficacy scales (e.g., task and barrier) [38].

Program Evaluation Survey (Childcare Providers). Childcare providers from the experimental condition will complete a survey (Appendix C) at post-intervention to gather information to evaluate implementation of the policy. Specifically, their initial willingness to participate (one item), preparedness (one item), and the feasibility or ease of policy implementation (18 items), will be rated on a scale from 1 (strongly disagree) to 5 (strongly agree). Future implementation will be assessed via 17 items rated from 1 (not at all likely) to 5 (extremely likely), and communication (four items) will be rated from 1 (not at all effective) to 5 (extremely effective). Nine open-ended response questions will capture aspects of the policy that the childcare providers liked the most, those that they found to be most/least important, challenges encountered, solutions used, any modifications made, the noted success of modifications, and their overall experience with policy implementation. The tool was created for the purposes of this study.

Interviews (Childcare Providers). As this is a pilot study, interviews will be completed with interested childcare providers (*n* ≈ 8–10) from the experimental condition. Using a semi-structured interview guide (Appendix B), these in-depth discussions will provide a greater understanding of the appropriateness of the policy, the feasibility of implementation, and suggestions for improvements that add to what is captured in the program evaluation survey. Following implementation of the eight-week policy intervention, childcare providers will be invited to participate in an interview (in person or via telephone), which will be audio recorded and transcribed verbatim.

Childcare Environment (Childcare Providers and Directors). The validated Environment and Policy Assessment and Observation—Self-Report (EPAO-SR; [39]) instrument examines the classroom physical environment and physical activity practices in childcare centres; this tool consists of two subscales, Space, Equipment, and Environment (eight items) and Practices around Physical Activity (three items). We will adapt the tool to conform with the Canadian context and remove the nutrition content (as seen in Ott et al.’s paper) [22]. This tool will be administered to childcare providers once during each week of data collection. The information solicited from this questionnaire will provide useful context to help better understand each classroom’s physical activity environment and practices and whether these change after the policy is implemented. The EPAO-SR Today [39], which entails six subscales (Morning Outdoor Activities (seven items); Morning Indoor Activities (eight items); Nap/Rest Time (three items); Afternoon Outdoor Activities (seven items); Afternoon Indoor Activities (three items); and Other Activities (three items)) will also be completed by one childcare provider per classroom on one chosen day at each data collection time point. This validated tool provides a snapshot of the specific activities in which the children engaged during morning and afternoon indoor and outdoor periods. Finally, the validated Director General EPAO-SR [39], which consists of two subscales (Childcare Environment (six items) and Physical Activity Policies (11 items)) also adapted for use in Canada without the nutrition subscale, will be administered to all centre directors at baseline. This will assess the presence of any existing physical environment characteristics that may inhibit or promote physical activity, and existing policies related to physical activity and sedentary time that may exclude a centre from participating in the study.

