### 2.4. Recruitment and Randomization

To secure an adequate sample size, this study will be conducted in eight randomly selected childcare centres (i.e., the clusters) chosen from an online listing of 55 eligible licensed childcare centres in London, Canada. Since it is necessary to implement the policy at the centre-level to groups of children, the childcare centres (i.e., the clusters) rather than the individual participants, will be randomly allocated by the project coordinator to either implement the physical activity policy (experimental; *n* = 4), or maintain their daily programming (control; *n* = 4) for the eight-week intervention period (at which time the policy will no longer be enforced).

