While Alberta has demonstrated that new accreditation standards show promise in improving activity levels among young children [26], this research will be the first to explore the feasibility and effectiveness of an institutional-level written childcare policy intervention as a mechanism to support improved physical activity levels (and minimize sedentary time) among young children in Ontario. By providing specific, evidence-informed guidance that offers strategies for achieving success at increasing physical activity and reducing sedentary time, childcare providers will be in a better position to ensure their programming is in line with Canadian recommendations [48]. Moreover, this study will offer an understanding of the uptake and receptivity of childcare centres to implementing such a policy, and feasibility and the burden of doing so. If effective, and appropriate to implement, the findings from the Childcare PLAY Policy study have the potential to guide institutional-level policies (short-term) and higher-level regulatory amendments to provincial standards (long-term). The effectiveness of the intervention rests in the creation of a physical activity policy that childcare providers believe is important and feasible to implement and aligns with their current curriculum and pedagogy. The results of the Childcare PLAY Policy will be shared with participants and childcare professionals and stakeholders via publications, infographics, and presentations.

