## Figures and Tables

**Table 1 ijerph-16-04400-t001:** Inclusion and exclusion criteria for the Childcare PLAY Policy study.

Participant	Inclusion Criteria	Exclusion Criteria
Childcare Centres	Centre-based facility in London, Canada At least one toddler or preschool classroom Childcare providers willing to participate ≥8 children who received parental consent English-speaking centre Does not currently have an institutional-level PA policy	Home-based childcare or after-school care only Not located in London, Canada or surrounding area Do not have a toddler or preschool-age classroom Childcare providers not willing to participate <8 children with parental consent Not an English-speaking facility Already has an established institutional-level PA policy
Childcare Providers	Full-time childcare provider in a toddler/preschool classroom Speaks and writes English	Not full-time Not a childcare provider in a toddler/preschool classroom Does not speak/write in English
Toddler/ Preschool Participants	Enrolled at a participating childcare centre 18 months–4 years Expected to remain at centre for next eight months Enrolled in a toddler/preschool classroom Parent/guardian speaks and understands English Has parental/guardian consent	Not enrolled at a participating childcare centre Not 18 months–4 years Not expected to remain in care for next eight months Not enrolled in a toddler/preschool classroom Parent/guardian does not read/write in English No parental/guardian consent

*Note.* PA = physical activity.

**Table 2 ijerph-16-04400-t002:** Outcome assessments for the Childcare PLAY Policy study.

Participant/Tool		Control Condition				Experimental Condition			
		Baseline (week 0)	Mid-Int (week 4)	Post-Int (week 9)	6M	Baseline (week 0)	Mid-Int (week 4)	Post-Int (week 9)	6M
Toddlers/ Preschoolers	Parent/Guardian Demographic Q	x				x			
	Physical Activity/ Sedentary Time (ActiGraph™ data)	x	x	x	x	x	x	x	x
	Anthropometrics	x				x			
Childcare Providers	Demographic Q	x				x			
	Policy Adherence Log (week 1–8) *		x				x		
	Program Evaluation Survey							x	
	Interview							x	
	EPAO-SR General	x	x	x	x	x	x	x	x
	EPAO-SR Today	x	x	x	x	x	x	x	x
	Self-Efficacy Q	x	x	x	x	x	x	x	x
Directors	Director General EPAO-SR	x				x			

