### SECTION 1: FEASIBILITY (i.e., ease of implementation) OF POLICY IMPLEMENTATION

1. Please, rate the degree to which you agree or disagree with the following statements about the PLAY policy.

	**Strongly Disagree**		**Neither Agree or Disagree**		**Strongly Agree**
a. When first approached to participate, I was very receptive to implementing the PLAY policy.	1	2	3	4	5
b. I felt adequately prepared to implement the PLAY policy.	1	2	3	4	5
c. The PLAY policy was easy to implement.	1	2	3	4	5
d. It was not easy to encourage children to engage in physical activity frequently throughout the day.	1	2	3	4	5
e. It was easy to encourage children to engage in higher intensity energetic play frequently throughout the day.	1	2	3	4	5
f. It was easy to provide children with the opportunity to achieve a minimum of 40 minutes of higher intensity energetic play each day.	1	2	3	4	5
g. It was not easy to expose children to a variety of indoor physical activities each day.	1	2	3	4	5
h. It was easy to expose children to a variety of outdoor physical activities each day.	1	2	3	4	5
i. It was easy to provide unstructured or child-directed free play each day.	1	2	3	4	5
j. It was not easy to provide structured or teacher-facilitated active play each day.	1	2	3	4	5
k. It was easy to offer a minimum of 120 minutes of outdoor time each day.	1	2	3	4	5
l. It was easy to provide the opportunity for children to engage in active play indoors when outdoor play was not possible.	1	2	3	4	5
m. It was not easy to provide shorter, more frequent outdoor play sessions.	1	2	3	4	5
n. It was easy to encourage continued energetic play through structured or teacher-led activities.	1	2	3	4	5
o. It was easy to encourage continued energetic play through teacher participation in physical activity.	1	2	3	4	5
p. It was not easy to encourage continued energetic play using verbal prompts.	1	2	3	4	5
q. It was easy to support children’s development of physical literacy through encouragement of fundamental movement skills (e.g., running, skipping, hopping, or jumping).	1	2	3	4	5
r. It was easy to avoid using my own screen-based technology when the children were present.	1	2	3	4	5
s. It was easy to avoid children’s exposure to screen-based technology during childcare hours.	1	2	3	4	5
t. It was not easy to break up children’s sedentary time by providing indoor active play opportunities.	1	2	3	4	5

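### Initial willingness is recalled at week 9 by experimental-arm providers from centres admitted on provider willingness, so alone it cannot show how receptive childcare centres are

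*Protocol article*

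**What the plan says.** Section 2.7 of the protocol article states: "Childcare providers from the experimental condition will complete a survey (Appendix C) at post-intervention to gather information to evaluate implementation of the policy". The same section dates that visit as "post-intervention (week 9"), and Table 2 marks the survey in the experimental arm at that visit only. The survey opens with two single-item ratings on a 1 to 5 scale: "Specifically, their initial willingness to participate (one item), preparedness (one item"). Appendix C, Section 1, item a words the first of these as "When first approached to participate, I was very receptive to implementing the PLAY policy".

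Table 1 lists, among the exclusion criteria for centres, "Childcare providers not willing to participate", with the mirror-image inclusion criterion beside it. Section 2.4 says the trial runs in "eight randomly selected childcare centres (i.e., the clusters) chosen from an online listing of 55 eligible licensed childcare centres", four per arm.

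The Discussion (Section 3) then says that "this study will offer an understanding of the uptake and receptivity of childcare centres to implementing such a policy". Section 2.8 reports the survey ratings as means and standard deviations.

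**The concern.** Item a asks about a moment before the trial began, but the answer is collected after eight weeks of running the policy. A provider for whom those weeks went well, or badly, may recall the first approach differently. The item also sits in the same block as 18 ratings of how easy the policy was, so part of any association between early receptiveness and later ease could come from hindsight.

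The respondents were also filtered on a closely related trait, because a centre with unwilling providers does not enter. Control-arm providers, who were approached as well, are never asked.

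Feasibility is the primary aim, and Section 1 defines it partly as the policy being well received by providers. Item a is the survey's only rating of initial reception. The Discussion speaks of childcare centres in general and looks ahead to institutional policy and provincial standards. If the mean of item a were offered as evidence for that statement, it would carry a selection effect and a recall effect that the trial cannot measure.

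**Working it through.** The plan gives no figure for this point, so there is none to reproduce. The check sets the sections side by side and then illustrates the direction and possible size of the selection effect.

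**Side by side**

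| Question | Where | Answer |
|---|---|---|
| Who may enter? | Table 1 | Only centres with willing providers |
| Who is asked item a? | Section 2.7, Table 2 | Experimental-arm providers |
| When? | Section 2.7, Table 2 | Once, at week 9 |
| What state does it describe? | Appendix C, item a | The first approach, before the policy |
| What is it to inform? | Section 3 | Receptivity of childcare centres |

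The survey's structure agrees with the text. Appendix C, Section 1 runs from a to t, which is 20 items and equals 1 + 1 + 18. With 17 continuation items and 4 communication items there are 20 + 17 + 4 = 41 rated items, of which item a is one.

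**Other sources on reception**
- The adherence log (Section 2.7) is kept three times a week in weeks 1 to 8, with full, partial and no adherence and reasons. It can show poor reception, but only inside enrolled centres.
- The ease items, continuation items and open questions (Appendix C) can also come out unfavourably. They too are asked at week 9 in the experimental arm.
- The interview guide (Appendix B) asks how receptive staff were. Interviews follow the intervention and involve about 8 to 10 interested experimental-arm providers.

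All of these describe the enrolled experimental centres. None undoes the selection at entry.

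**Illustration of the selection effect**

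The inputs are assumptions, not taken from the documents: receptivity among everyone approached is normal with mean 3 and SD 1; a fraction r accept; receptivity correlates ρ with the propensity to accept. The expected mean among those retained is

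3 + ρ × φ(c) / r, where c is the standard normal quantile at 1 − r and φ is the normal density.

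Example: r = 0.5 gives c = 0, φ(0) = 0.399 and φ/r = 0.798. With ρ = 0.6 the mean is 3 + 0.6 × 0.798 = 3.48.

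| Acceptance r | ρ = 0 | ρ = 0.3 | ρ = 0.6 | ρ = 1.0 |
|---|---|---|---|---|
| 30% | 3.00 | 3.35 | 3.70 | 4.16 |
| 50% | 3.00 | 3.24 | 3.48 | 3.80 |
| 70% | 3.00 | 3.15 | 3.30 | 3.50 |
| 90% | 3.00 | 3.06 | 3.12 | 3.19 |

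The shift is upward for any positive correlation and zero without one. Over this grid it runs from 0 to 4.16 − 3 = 1.16 points. The article gives neither r nor ρ, and the model ignores the bounds of the 1 to 5 scale, so the table shows direction and range only. It does not cover hindsight, which could act in either direction.

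**The case against.** A reader might infer that a favourable result is built into the design and that item a must be high whatever centres really think. The documents do not support that. Table 1 asks for willingness to take part in a trial, in either arm. Item a asks each provider how strongly they welcomed the policy itself. These are different things, and individual answers can vary and be low.

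A reader might also infer that the promised understanding of uptake and receptivity rests on this one item. It does not: the log, the ease and continuation items, the open questions and the interviews all bear on it and can be negative. Item a is one of 41 ratings, summarised by a mean and SD, with no test, threshold or progression decision attached in the article.

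A third tempting step is to size the problem through recruitment. If eight centres came from 8, 12, 16 or 24 approached, acceptance would be 100%, 67%, 50% or 33%. Those denominators are assumptions, and they measure agreement to join a study, whereas the Discussion speaks of uptake of implementing a policy. Nor would item a be the same in each case: if receptivity drives acceptance, the retained mean moves with the acceptance rate, as the table shows.

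Other parts of the defence also stand. Studying only consenting centres is inherent in a trial. An article may leave the tally of refusals to the participant flow, so its silence there is no error. Whether preparation was adequate can reasonably be judged after using the policy, and the article does not say that item b serves as a check on the training.

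The defence does not remove the mismatch between what item a describes and when it is asked, or the gap between the group asked and the centres the Discussion refers to.

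**Conclusion.** The point holds in a limited form. Item a is a retrospective rating from a selected group. It is open to hindsight and is likely biased upward by selection, by an amount the documents do not allow anyone to estimate. The range of zero to about 1.2 points rests wholly on the assumed mean, SD, acceptance rate and correlation. The upward direction rests on one assumption: that more receptive providers are more likely to be in centres that join.

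Item a cannot by itself support a statement about the receptivity of childcare centres. Read with the log, the other survey items and the interviews, it can contribute to a description of reception in the four experimental centres. The accelerometer outcomes and the sample size are not affected.

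**What to change.** 1. Ask item a before the policy starts. Table 2 already has providers in both arms completing a demographic form and the self-efficacy questionnaire at baseline; either can carry the item. Ideally it is answered before allocation is known; the article does not state the order of baseline measurement and allocation. A self-completed form is preferable to the training session, which the project coordinator leads and which is described only for the experimental arm.
2. Leave item b at week 9. If preparedness is to be read as a check on the training, add one rating before the policy begins.
3. Limit the receptivity sentence in the Discussion to centres that agreed to take part, and read it beside the numbers of centres approached and declining in the participant flow.

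The cost is one item moved or added in an existing form (two if preparedness is also rated early), with no extra visit or participant, and a narrower conclusion. Earlier timing removes hindsight about the policy, but not selection at entry, which must still be stated as a limitation.

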The primary aim of the eight-week Childcare PLAY Policy study is to evaluate the feasibility of an evidence-based, stakeholder-informed, written physical activity and sedentary time policy in childcare centres. For the purpose of this study, feasible refers to the intervention being implemented as intended and well received by childcare providers. Specific objectives include determining whether the policy was effective at: (i) increasing young children’s (i.e., toddlers and preschoolers, age 18 months–4 years) physical activity (i.e., MVPA and total physical activity (TPA)); (ii) reducing young children’s sedentary time; (iii) producing a feasible and appropriate policy for use in the childcare setting; (iv) increasing childcare providers’ self-efficacy for facilitating young children’s physical activity during childcare; and (v) producing environmental changes in support of physical activity in childcare. Because the implementation of a policy may influence other aspects of the childcare, an environmental assessment will also be conducted. This pilot study will evaluate the feasibility and effectiveness of policy implementation within individual childcare centres, and it will afford the opportunity to modify the policy prior to examining its effectiveness in a larger, more diverse sample.

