### 2.8. Analysis

All data will be entered, verified, and stored in our lab. Baseline characteristics of the children and the childcare centres will be summarized descriptively; participant characteristics for those who complete the study and those who drop out will be explored. All statistical analyses will be performed in R [31], using the lme4 [40] and lmerTest packages [41].

Implementation Log. Frequencies and percentage scores will be calculated to reflect adherence to policy statements and reasons that compliance was not attained will be reported descriptively.

Program Evaluation Survey and Interviews. Means and standard deviations of survey item ratings will be provided. Responses to open-ended program evaluation survey and interview questions will be analyzed using thematic content analysis [42] using QSR NVivo.

Physical Activity. Children’s physical activity data will be analyzed using a series of linear mixed effects models for each of the three outcome variables (i.e., TPA, MVPA, and sedentary time). Group (experimental versus control) and time (baseline, mid-intervention, post-intervention, and six-months post-intervention) will be modelled as a fixed effect, and will be evaluated using *t*-tests, with a Satterthwaite approximation determining degrees of freedom. Descriptive survey data will be analyzed using frequencies, *t*-tests, and chi-square tests.

Childcare Providers’ Self-Efficacy. Descriptive statistics will be reported to indicate changes in childcare providers’ self-efficacy specific to implementing physical activity in childcare. Classical test theory will be used to assess internal consistency of the scales, exploratory factor analysis will be used to assess the factorial validity of the measured constructs, and item response theory will be used to explore the item and scale characteristics of the measurements used to assess the two polytomous constructs in this study (i.e., task and barrier self-efficacy). Factor analysis and classical test theory analyses will be undertaken within the psych package [43] and the ltm package [44] will be used for the item response theory analyses.

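### How well providers received the policy is measured only after the eight weeks, by one survey and volunteer interviews, so early leavers and reluctant rooms may be under-represented in the primary objective

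*Protocol article*

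**What the plan says.** Protocol article, 1. Background, sets the objective: "The primary aim of the eight-week Childcare PLAY Policy study is to evaluate the feasibility" of a written policy. The same section defines the term: "feasible refers to the intervention being implemented as intended and well received by childcare providers". The definition has two parts, called delivery and reception here. No numerical criterion is attached to either.

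Three sources inform it, all described in 2.7. Measures:

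- **Adherence log (mainly delivery).** "A log will be completed by childcare providers three times per week" over the eight weeks, with *yes*, *part* or *no* for each policy statement and a reason when a statement was not followed. Under 2.8. Analysis, "Frequencies and percentage scores will be calculated to reflect adherence to policy statements", and the reasons are reported descriptively.
- **Program evaluation survey (mainly reception).** "Childcare providers from the experimental condition will complete a survey (Appendix C) at post-intervention". Table 2 shows one administration, at week 9. Item ratings are summarised by means and standard deviations.
- **Interviews (mainly reception).** "interviews will be completed with interested childcare providers", about 8–10 of them, from the experimental arm. Invitations go out after the eight weeks, and the interviews are meant to add to the survey.

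2.8. Analysis also says that the characteristics of completers and drop-outs will be explored.

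**The concern.** Both sources on reception come after the intervention has ended, and the interviews are filled by people who put themselves forward. The article gives no earlier occasion for a provider who leaves or abandons the policy part-way to complete the survey. Nothing in the stated interview rule prevents most of the 8–10 interviews from coming from one or two enthusiastic centres. Comparing the characteristics of drop-outs with those of completers does not bring the drop-outs' opinions into the feasibility result.

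Selection also begins before the trial does: Table 1 excludes centres whose providers are unwilling to take part.

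The interviews carry some weight of their own. The survey description in 2.7 says that the open questions cover what providers found most and least important. Appendix C as printed asks only about the most important part, although it does ask about challenges and desired changes. The direct question on the least appropriate features is in the interview guide (Appendix B, question 4), which only volunteers answer.

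The background section says that the pilot is an opportunity to revise the policy before a larger study. Providers who found it unworkable hold much of the information needed for that revision. With no numerical criterion for feasibility, the conclusion depends heavily on whose accounts are collected.

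**Working it through.** The plan states no feasibility threshold, no number of providers and no provider or room attrition rate, so it has no figure to reproduce. The only loss figure, 20% in 2.3. Sample Size, concerns children and accelerometer compliance and cannot be carried over to staff.

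**Who can contribute, by source**

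| Source | When | Provider or room that stops in, say, week 4 |
|---|---|---|
| Log | Weeks 1–8, three days a week | Entries up to then count; if logging continues, stopping is recorded as *no* |
| Survey | Week 9 only | Not excluded by the text, but no provision to reach someone who has left |
| Interview | After week 8, volunteers | Can volunteer, but is not deliberately sought |

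**Log schedule (from the document).** 8 weeks × 3 days = 24 log days. With 8 policy statements, 24 × 8 = 192 scheduled entries per log. Delivery is therefore observed well before week 9.

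**Survey, illustration only.** Let *s* be the share of experimental-arm providers missing at week 9 and *d* the amount by which their ratings would fall below those of responders. Then upward bias in the mean = *s* × *d*. Both inputs are assumed.

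| | *d* = 0 | *d* = 1 | *d* = 2 |
|---|---|---|---|
| *s* = 10% | 0 | 0.10 | 0.20 |
| *s* = 20% | 0 | 0.20 | 0.40 |
| *s* = 30% | 0 | 0.30 | 0.60 |

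A negative *d* (missing providers more favourable than responders) would reverse the sign.

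**Log, illustration only.** Assume 80% adherence on returned entries, a share *s* of rooms that stop after week *w* and return nothing more, and missing entries counted as not followed. Adherence over scheduled entries = (1 − *s*) × 0.80 + *s* × 0.80 × *w*/8.

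- *s* = 10%, *w* = 6: 0.72 + 0.06 = 78%
- *s* = 20%, *w* = 4: 0.64 + 0.08 = 72%
- *s* = 30%, *w* = 2: 0.56 + 0.06 = 62%

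Against the 80% on returned entries, the gap is 2 to 18 percentage points. This is a lower bound for adherence, because a missing log does not prove that the policy was not followed.

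**The case against.** A reader might infer that feasibility as a whole is judged at week 9, from staff still in post, and is therefore overstated. The documents do not support that.

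- The log is the direct measure of delivery. It runs through weeks 1–8 and records partial and failed adherence with reasons. This stands, and it limits the point to reception.
- The survey is addressed to experimental-arm providers without restriction. That only those still in post would answer is an inference from its timing. This stands; the text merely makes no arrangement for leavers.
- Overstatement is not shown. No attrition figure is given, providers are full-time, the period is eight weeks, and dissatisfied staff may also volunteer for interview. This stands: the most one can say is that reception may be overstated.
- Interviews always need willing participants, and volunteer sampling is ordinary in a supplementary qualitative component. This is fair, but it does not prevent invitations from being spread across centres and rooms.
- The denominator for the adherence percentages and the handling of missing logs are details that an article may leave to a fuller document. This stands, so the log is only a supporting step here.

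What the objection does not remove are two rules that the article itself states: a single survey at week 9, and interviews with interested providers after the eight weeks. Both can lose views in the same direction on half of the primary objective.

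**Conclusion.** The point holds in a limited form. The reception half of the primary objective is measured only after the eight weeks, from sources that may under-represent providers who left or stopped and may over-represent keen centres. Reception may be overstated, but the documents do not allow the size to be estimated. The illustrations (0 to 0.6 points on the survey mean, 2 to 18 percentage points on adherence) rest wholly on assumed attrition, rating gaps and stopping times. If missing providers rate as responders do, the survey bias is zero. For delivery, the log partly offsets the concern. This is an inexpensive improvement worth making, not a flaw that invalidates the feasibility evaluation.

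**What to change.** 1. **Interviews.** Keep 8–10. Invite so that each of the four experimental centres is represented, and deliberately approach rooms that stopped or had low logged adherence. Set no fixed quota for such rooms, since that would swap one selection for its opposite. Report who was invited and who declined.
2. **Survey.** Offer the existing Appendix C survey to any experimental-arm provider at the time of leaving or stopping the policy. The lead-in to its Section 2 assumes that implementation has formally ended and needs rewording for leavers. Appendix C promises anonymity, so report any reasons for stopping only in aggregate.
3. **Log (supporting step).** Show adherence over all scheduled log days (3 × 8 = 24 per log) beside the figure for returned logs, with missing logs as their own category.

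Cost: no new instrument and no additional interviews, but slightly more coordination. Some low-adherence providers may decline, and reported feasibility may look less favourable.
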